### Potential Technologies for Measuring Adherence to Home Shoulder Physiotherapy

Several technologies have been developed and pilot tested to provide more objective and complete assessments of adherence to home physiotherapy [13,15,65-72], but none have been validated in a clinical population. The common premise underlying a technical solution to adherence monitoring is using sensors to record patient home physiotherapy and have a computer algorithm classify activity type and potentially evaluate the technique. Various sensors have been investigated for this application, including video and depth sensors [65-68], strain sensors mounted on elastic bands [13], and inertial sensors [15,69-72].

Inertial sensors include accelerometers, gyroscopes, and magnetometers. These sensors are combined in small, inexpensive integrated circuit packages called inertial measurement units (IMUs). IMUs are found in smartphones, smart watches, and GPS devices, and they enable ongoing navigation with loss of GPS signals (eg, indoors). Advances in the capability of these sensors have enabled their use in demanding clinical applications, such as upper extremity motion tracking [73], clinical shoulder evaluation [74-77], kinematic analysis [78-82], and shoulder physiotherapy adherence evaluation [15,69,70].

Inertial sensors are, in our opinion, an ideal method for measuring adherence to home shoulder physiotherapy. These sensors are already integrated into robust, accessible devices, such as smart watches, facilitating low-cost deployment. Such wearable devices are unobtrusive and easy to use anywhere, unlike solutions based on video capture. Finally, they are highly accurate for this task [15] and can theoretically be used to measure adherence to any exercise involving motion.

Several studies have investigated the potential for shoulder physiotherapy adherence evaluation using inertial sensors in the laboratory setting. McGirr et al [69] used a 3-axis gyroscope to classify 3 shoulder exercises performed with an elastic band and were able to classify activity type, but with relatively low accuracy (86%-91%). Pan et al [70] used classical ML techniques to classify 5 different shoulder exercises from multiple synchronized inertial sensors mounted on the chest, upper arm, and wrist, achieving classification accuracy of 96.9% in the laboratory setting. Our pilot study used state-of-the-art deep learning algorithms to classify 7 evidence-based physiotherapy exercises from a single wrist-worn IMU in a commercial smart watch with an accuracy of 99.99% [15].

Deep learning is a class of ML algorithms for training deep hierarchical models, such as artificial neural networks (ANNs), which are ML models partly inspired by biological neural networks found in animal brains [83]. Recent advances in deep learning and computer performance have together spurred revolutionary developments in the capabilities of modern artificial intelligence systems [84]. In our pilot work, we demonstrated that deep learning significantly outperforms classical ML algorithms for inertial exercise classification [15]. Unlike classical ML models, neural networks can also benefit from transfer learning [85], which facilitates network retraining and updating in various contexts, such as adding a new exercise class or patient to the training dataset. Although significant computational resources are required for training ANNs, trained ANNs can be compact and deployable with modest computer hardware [86]. The ML models we developed in our pilot work were designed for deployment and real-time operation on a smart watch, having only 300,000 parameters. This aspect of the SPARS design permits a highly reliable edge-computing system architecture, where end-user apps are always responsive and function independent of internet connectivity or cloud computing infrastructure.

### Ethical and Policy Issues Related to Measuring Adherence to Patient Self-Management Strategies

There are a number of ethical and policy issues raised by the proposed project that will be examined in detail, concurrent with the clinical validation of the SPARS technology. Building on our past work addressing the challenges of introducing innovative digital health technologies [87], this analysis will inform the design and use of SPARS in the delivery of adherence-driven care. Drawing on the critical bioethics of Hedgecoe [88], we will examine the actual lived experiences and policy realities that are implicated in SPARS deployment and program development. However, we can anticipate, based on the bioethics literature, that issues at the intersection of ethics and policy will be raised in 3 distinct areas.

First, the act of surveillance introduces a number of ethical challenges. One is that surveillance stands to influence the behavior of participants, despite the conflicting evidence on the ways in which the proposed *Hawthorne effect* might occur [89]. Beyond a simple form of data collection, however, the collection of ubiquitous data about movements could have a number of unanticipated consequences [90]. A potential effect is to enhance the frequency or quality with which exercises are performed, but others include the distrust of the technology and health care providers who ultimately observe the data. Where participants might feel coerced into completing a form of physical activity, especially in cases where workplace injuries are involved, resistance might be substantial [91]. These are ethically important challenges that need to be addressed throughout this program and will dictate what data are collected, how they are controlled, and how and to whom the analysis results are presented.

Second, the surveillance and related project data promise to generate insights about which types of patients engage in exercises with the greatest fidelity. Findings related to patient profiles of those who engage and those who do not could be used in a variety of ways, including reallocating resources to those who stand to benefit from high engagement or enhanced behavioral change programs for those who do not engage. Generally, these questions of resource allocation relate to the priority-setting process for rehabilitation programs [92] and require detailed analysis to inform policy.

Third, the algorithms being deployed in this study are developed by individuals with particular views of the world. The types of data being used to train the algorithms, assumptions about the functioning of the technology, and beliefs about appropriate outputs are all shaped by the education, race, gender, and other social realities of the people writing the computer code. These points relate to bias that could potentially be built into the algorithm itself and the fairness of its outputs [93].

Each of these points will form a substantive focus on the ethical and policy analyses that are part of this study.

### Specific Research Aims

The specific research aims, and related objectives and hypotheses for this study are detailed below.

#### Aim 1: Develop and Validate the Smart Physiotherapy Activity Recognition System For Evaluating Shoulder Physiotherapy Adherence

##### Objectives

The related objectives are as follows:

Inertial sensor data are collected during supervised physiotherapy for 120 patients with rotator cuff pathology over full treatment duration (up to 5 months).Technical failures preventing supervised data collection are less than 5%.The SPARS artificial intelligence is trained to classify physiotherapy exercise type and technique with classification accuracy exceeding 90% and 80%, respectively.

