#### Inertial Data Labeling

The researchers will attend a supervised physiotherapy session for each patient once every 2 weeks to record exercise type and technique labels synchronously with inertial data collection, based on the input from the treating physiotherapist. The technique will be labeled as a binary variable, indicating if the treating physiotherapist was satisfied that the exercise was performed correctly (as intended). The treating physiotherapist will also make a record of prescribed home exercises and exercise type and technique evaluations at each supervised physiotherapy session.

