#### Smart Physiotherapy Activity Recognition System-Home Physiotherapy Technique Adherence

A second supervised learning algorithm will be trained, validated, and optimized to classify the exercise technique from the labeled inertial sensor data collected during the supervised physiotherapy sessions. We anticipate that a CRNN architecture similar to the exercise type classifier will likely be suitable. The validated technique classifier will be used to evaluate the technique adherence from the inertial data collected during unsupervised home sessions.

Anticipated challenges with the proposed supervised learning approach to technique evaluation include class imbalance and recovery-related changes in exercise performance. It is anticipated that many more correct technique training examples may be available for some exercises and that an exercise may be performed incorrectly in ways not observed during the supervised sessions, leading to class imbalance. It is also anticipated that through recovery, the expectation for technique and performance of an exercise may change over time, creating a moving target for the technique classifier. The challenge of class imbalance may be mitigated using several potential approaches including (1) random over and undersampling [117]; (2) cost-sensitive learning [117]; (3) semisupervised learning [118]; (4) anomaly detection [119,120]; and (5) synthetic data augmentation [121]. The challenge of recovery-related performance changes may be mitigated by providing our technique classifier metadata related to the classification task (eg, treatment week, pathology, and surgery) [116], implementing patient-specific ML models using transfer learning, and periodically retraining the ML models through recovery.

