#### Construct Validity

The construct validity of the SPARS adherence measures will be evaluated using cross-validated exercise type and technique classification performance metrics (accuracy, precision, recall, and f1-score) from the labeled inertial data. The cross-validated metrics will be assessed for 3 different fold splitting strategies: (1) by-subject; (2) by-session; and (3) within-session. Respectively, these estimate SPARS performance for (1) new subjects (with no training data); (2) new sessions for subjects with prior training data; and (3) new exercise repetitions within a session from which training data were acquired. The by-session cross-validation most closely approximates the use case in the proposed study and will benchmark SPARS performance against our stated measurable objectives.

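### The technique classifier's only numerical target is raw accuracy above 80%, which does not show that it can detect incorrect technique if correct labels predominate

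*Protocol article*

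**What the plan says.** Among the Aim 1 objectives, the article states that the system is to be trained to "classify physiotherapy exercise type and technique with classification accuracy exceeding 90% and 80%, respectively". The second figure, 80%, is the only number in the article against which technique classification is judged.

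Under Inertial Data Labeling, the outcome has two classes: "The technique will be labeled as a binary variable, indicating if the treating physiotherapist was satisfied that the exercise was performed correctly".

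The section on technique adherence foresees imbalance from two sources. One is that "It is anticipated that many more correct technique training examples may be available for some exercises". The other is that "an exercise may be performed incorrectly in ways not observed during the supervised sessions, leading to class imbalance". On handling it, the section says "The challenge of class imbalance may be mitigated using several potential approaches" and lists resampling, cost-sensitive learning, semisupervised learning, anomaly detection and synthetic augmentation.

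Construct Validity plans accuracy, precision, recall and f1-score under three ways of splitting the folds. It singles out the by-session split as the one that "will benchmark SPARS performance against our stated measurable objectives". For technique, those objectives contain accuracy only. Concurrent Validity adds a comparison of the system's technique evaluations with physiotherapist logs, without a criterion for passing.

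**The concern.** With two unequal classes, raw accuracy is a weighted mean of the two class recalls, and the weights are the class shares. If correct repetitions dominate the labelled data, the figure says much about how well correct technique is recognised and little about how often incorrect technique is caught. Catching incorrect technique is the purpose of this classifier.

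The imbalance remedies listed in the article act on training. They do not alter the criterion by which the result is judged, and they are optional.

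At stake are both Aim 2 hypotheses in so far as they concern technique: that technique is better in supervised sessions than at home, and that technique adherence is associated with clinical outcomes. A classifier that seldom flags errors would score technique as nearly perfect in both settings. A null finding could then reflect the instrument and not the patients.

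**Working it through.** **Inputs.** From the article: the technique target (accuracy above 80%), the binary label, and anticipated imbalance towards correct technique for some exercises. Not in the article: the share *p* of evaluated technique labels that are correct. I treat *p* as an assumption and show a range. The 80% target is a chosen figure with no derivation, so there is nothing to reproduce.

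**Identity.** Let *a* be the recall for correct technique and *b* the recall for incorrect technique.

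- Accuracy = *p* × *a* + (1 − *p*) × *b*
- Balanced accuracy = (*a* + *b*) / 2

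**Limiting case: always answer 'correct'.** Here *a* = 1 and *b* = 0, so accuracy = *p* and balanced accuracy = (1 + 0)/2 = 50%.

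| Assumed *p* | Accuracy | Exceeds 80%? | Recall, incorrect | Balanced accuracy |
|---|---|---|---|---|
| 0.70 | 70% | no | 0% | 50% |
| 0.80 | 80% | no | 0% | 50% |
| 0.81 | 81% | yes | 0% | 50% |
| 0.85 | 85% | yes | 0% | 50% |
| 0.90 | 90% | yes | 0% | 50% |
| 0.95 | 95% | yes | 0% | 50% |

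The constant rule passes only when *p* is above 0.80. At exactly 0.80 it fails, because the objective requires accuracy to exceed the figure.

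**A classifier that has not collapsed.** Take *p* = 0.90, *a* = 0.85, *b* = 0.40. Accuracy = 0.90 × 0.85 + 0.10 × 0.40 = 0.765 + 0.040 = 0.805. It passes while missing 60% of incorrect repetitions. Its balanced accuracy is (0.85 + 0.40)/2 = 62.5%.

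**Ordering of classifiers.** Take *p* = 0.85, *a* = 0.79, *b* = 0.80. Accuracy = 0.85 × 0.79 + 0.15 × 0.80 = 0.6715 + 0.12 = 0.79, which fails. The constant rule scores 0.85 and passes. Balanced accuracy puts them in the sensible order, 79.5% against 50%, although 79.5% also falls just short of 80%.

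**Below 80% correct.** With *a* = 1, the recall for incorrect technique at which accuracy equals 80% is (0.80 − *p*)/(1 − *p*). That is 0.10/0.30 = 33% at *p* = 0.70 and 0.05/0.25 = 20% at *p* = 0.75. The target therefore tolerates weak detection even where the constant rule fails.

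**What balanced accuracy would guarantee.** If (*a* + *b*)/2 exceeds 0.80 and neither recall can exceed 1, each recall must exceed 2 × 0.80 − 1 = 60%, whatever *p* is.

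**Effect on the supervised-versus-home comparison.** Suppose both settings are scored by the classifier with the same recalls (an assumption). If *q* is the true share of correct repetitions in a setting, the measured share is *q* × *a* + (1 − *q*) × (1 − *b*). The measured difference between settings is then the true difference times (*a* + *b* − 1). The multiplier is 0 for the constant rule and 0.85 + 0.40 − 1 = 0.25 for the second classifier. At a balanced accuracy of 80% it is 2 × 0.80 − 1 = 0.60.

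**The case against.** The strongest reply is that a classifier blind to bad technique would not go unnoticed. Recall and f1-score are planned. The comparison with physiotherapist logs, using paired tests, Bland-Altman plots and an absolute-agreement intraclass correlation, would show a bias towards correct technique. A constant technique score has no variance, so the regression under Criterion Validity could not be fitted. The authors also name class imbalance and list five remedies, which makes total collapse a limiting case and not a likely product of the plan. An article may also leave class-specific reporting to a fuller document.

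Much of this stands. A reader might infer that the plan expects mostly correct labels overall, or that a useless classifier would be declared validated. The text supports neither. It says only that correct examples may predominate for some exercises, gives no share, and nowhere makes accuracy above 80% sufficient on its own for validation. A reader might also extend the point to the 90% exercise-type target, but the imbalance discussed in the article concerns technique only. Nor can harm to care in the pilot be inferred, because how adherence information enters clinical decisions is left to later programme design.

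What does not stand is that the other checks close the gap. None carries a pass threshold, and the article does not say which class recall and f1-score refer to. Calculated on the correct class, the constant rule's f1-score at *p* = 0.85 is 2 × 0.85/(1 + 0.85) = 0.919, which looks excellent. The equalized odds and equal opportunity metrics under Algorithmic Fairness are met trivially by a constant classifier, since its class-conditional error rates are the same in every subgroup. The partly working classifier (85% and 40%) produces a score that varies, so the regression would run without warning. And the choice of target was not left to another document: the article fixes it.

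**Conclusion.** The concern holds in a conditional form. The article fixes one numerical criterion for technique, and that criterion can be met with little or no ability to detect incorrect technique. For a classifier with no such ability, the condition is that more than 80% of the evaluated labels are correct. The article anticipates imbalance in this direction but does not quantify it, so the 80.5% example at a 90% share illustrates the problem and does not forecast the result.

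Other planned metrics could expose a poor classifier, so this is a weakness in the stated objective and not proof that validation will fail. It should be fixed, because the technique hypotheses rest on a property that the objective does not test, but it does not invalidate the study.

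**What to change.** Restate the technique part of the Aim 1 objective as balanced accuracy, defined as the mean of the recalls for correct and incorrect technique, exceeding 80% under by-session cross-validation. Report the recall for each class and the majority-class rate beside raw accuracy. Leave the exercise-type target as it is.

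The cost is small: one objective is reworded, recall is already among the planned metrics, and no new data are needed. The downside is a less favourable headline figure and a harder target. The 80% cut-off was set for raw accuracy, so a sentence justifying it on the new scale would help. Separate minimum recalls for the two classes, or an f1-score for incorrect technique, would also make the criterion sensitive to the incorrect class.

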#### Aim 2: Measure the Rate of Adherence to Home Shoulder Physiotherapy, the Relationship Between Adherence and Recovery, and Identify Barriers to Home Physiotherapy Adherence

##### Objectives

The related objectives are as follows:

Inertial sensor data are collected during home physiotherapy for 120 patients with rotator cuff pathology over full treatment duration (up to 5 months).Technical failures preventing home data collection are less than 5%.Clinical outcomes: return to work status, shoulder range of motion, rotator cuff strength, and patient-reported outcomes of pain and disability are collected pretreatment, monthly through treatment (up to 5 months), and at 12-months final follow-up. The final follow-up exceeds 85%.A total of 23 potentially significant predictors of home physiotherapy adherence (identified in Methods: Barriers to Adherence) are collected for all study participants at the time of recruitment.

##### Hypotheses

The related hypotheses are as follows:

Exercise technique adherence is better for supervised sessions than at home (*P*<.05).There will be a statistically significant association (*P*<.05) between home physiotherapy exercise participation and technique adherence and the identified clinical outcomes.

#### Aim 3: Develop and Pilot Test a Conscientious Smart Physiotherapy Activity Recognition System–Powered Shoulder Rehabilitation Program That Provides Individualized Adherence-Driven Patient Care in Accordance With Ethical Innovation and User-Centered Design Practices

##### Objectives

The related objectives are as follows:

Conduct and analyze qualitative interviews with stakeholders and end users to identify functional needs and different perspectives on ethical commitments and challenges related to individual experiences, privacy, clinical decision making, health resource allocation, and policy.Develop novel shoulder rehabilitation strategies within the Working Condition Program, leveraging validated SPARS adherence analytics to conscientiously guide physiotherapy treatment as per the ethical, policy, and user-centered design analysis.Pilot test the rehabilitation program in 20 patients. Conduct postimplementation qualitative interviews to re-examine ethical, policy, and design issues.

##### Hypotheses

The methodology to be drawn upon for the service design process and qualitative evaluation is fundamentally inductive and user-driven. Therefore, it would not be appropriate to articulate specific hypotheses to drive our data collection. We have outlined several ethical and policy issues that we will address, but we will approach the participants in ways that encourage them to describe the experiences and issues most pertinent to their own viewpoints. In so doing, we will remain open to all insights that emerge from design activities and qualitative interviews.

## Methods

### Smart Physiotherapy Activity Recognition System Technical Development and Clinical Validation Study (Aims 1 and 2)

We will further develop SPARS to evaluate the physiotherapy exercise technique and validate the SPARS exercise type and technique evaluations in a clinical population undergoing physiotherapy treatment for rotator cuff pathology. The relationship between adherence and recovery and barriers to home physiotherapy adherence will also be determined in this clinical validation study.

#### Population

We will conduct a prospective longitudinal cohort study of 120 patients who have been referred to Sunnybrook Health Sciences Centre for the management of rotator cuff pathology. The inclusion criteria will be as follows: (1) age ≥18 years; (2) diagnosis of unilateral rotator cuff tendinosis, shoulder impingement syndrome, or degenerative or traumatic rotator cuff tear; (3) planned conservative or operative management; and (4) capacity to participate in home shoulder physiotherapy. Exclusion criteria will be as follows: (1) upper extremity neurologic deficit; (2) bilateral symptomatic rotator cuff pathology; and (3) failed surgical management of rotator cuff pathology.

#### Inertial Data Collection

Each study subject will be provided with a smart watch to be worn on their affected extremity when performing the prescribed physiotherapy exercise. The smart watch must be worn for all physiotherapy exercise sessions conducted over the duration of treatment, up to a maximum of 5 months. This includes all supervised physiotherapy sessions at the Holland Centre and any physiotherapy exercise sessions conducted by the patient independently (home exercises). No alteration to the prescribed physiotherapy will be undertaken during this clinical validation study.

The smart watches purchased for this study will have a 9-axis IMU (3-axis accelerometer, 3-axis gyroscope, and 3-axis magnetometer). The inertial sensors will be sampled at 50 Hz and recorded to the internal memory storage on the smart watch. The inertial data will be encrypted using the Rivest–Shamir–Adleman public-key cryptosystem. The smart watch will permit up to 150 hours of sensor data recording to its 4 GB internal memory. The sensor data will be retrieved and removed from the smart watch when the patient attends supervised physiotherapy at the Holland Centre (2 times per week).

